## 4. Discussion

To our knowledge, the PRIMD trial is the first adequately powered, placebo-controlled RCT evaluating the effect of probiotic supplementation on dysbiosis in infants of mothers with GDM and the risk of probiotic sepsis.

Given the adverse effects of maternal GDM on infants’ gut microbiota and neurodevelopment, it is important to assess this outcome in our trial [38,39,40,41]. The dynamic maturation of gut microbiota during infancy is affected by various factors, including maternal health (e.g., GDM), the delivery mode, the feeding pattern, gestational age, and exposure to medications [42,43]. The disruption of initial microbial colonization has been associated with risk of adverse neurodevelopment, allergies, obesity, and auto-immune disorders in later life [44]. Gut microbiota and their metabolites regulate neurodevelopment and cognitive functioning via the bi-directional communication system known as the GMB axis [45]. The GMB axis influences brain development and function via the hypothalamo–pituitary axis (HPA); the vagus nerve; immune signalling; the production of neurotransmitters; and the production of metabolites, such as SCFAs (butyrate, propionate, and acetate), bile acids, and tryptophan derivatives. SCFAs maintain and modulate both gut epithelial and blood–brain barrier (BBB) integrity [46,47,48]. They directly affect the brain, binding to local receptors and induce epigenetic modifications, thus modulating neuro-inflammation. Additionally, SCFAs’ enhance regulatory T cell function and activate the sympathetic nervous system and the vagus nerve. Indole, a tryptophan derivative, reduces neuro-inflammation and enhances gut epithelial and BBB integrity [49]. Bile acids influence the brain and HPA axis through specific local receptor modulation [50,51]. Gut microbiota can produce serotonin, dopamine, nor-epinephrine, histamine, and gamma-amino butyric acid (GABA) directly or indirectly via entero-endocrine cell stimulation in the gut epithelium. Bifidobacteria are known to produce GABA [52]. These neurotransmitters exert local effects through vagal stimulation and can directly affect the brain by traversing the BBB [53].

The association of microbiota composition and neurodevelopment has been reported in term infants not supplemented with probiotics. A recent study reported an association between increased levels of Bifidobacteria and Eggerthella and decreased levels of Streptococcus, and Hungatella, linked to a successful performance on the Point-and-Gaze attention test in 44 term infants at 4–6 months age [54]. Bonham et al. reported the influence of Klebsiella, *E. coli*, and Bifidobacteria in the gut in the first year of life and the prediction of cognitive function and brain growth via MRI [55]. Zhou et al. showed significantly higher neurodevelopmental scores at 6 months following vaginal microbiota transfer in 68 term infants born via caesarean section [56]. Furthermore, Bifidobacterial dominance in the first 1000 days of life has shown positive influences on cognition, adaptive behaviour, and communication in preterm-born children [57]. Given this evidence, probiotic supplementation may provide a pathway to modulate the GMB axis and improve neurocognition in infants of mothers with GDM.

GDM during pregnancy adversely impacts infant weight gain and increases the risk of obesity in the long term [54,55,56]. Obesity is a multifactorial disorder influenced by genetic, environmental, lifestyle factors, and possibly the microbiome [58,59,60]. Furthermore, the Developmental Origins of Health and Disease (DOHAD) hypothesis highlights the role of an unfavourable ‘in utero’ environment on long-term health, particularly metabolic syndrome and cardiovascular disease later in life [61,62,63,64]. The modulation of gut microbiota has been shown to be effective treatment for obesity and seems to be a promising strategy [65,66].

If proven effective in improving dysbiosis, future studies should investigate the optimal timing, dosage, strain, and duration of probiotic supplementation during the perinatal period in infants of mothers with GDM. Additionally, data linkage studies assessing the long-term effects of early microbiota modulation would provide evidence of the effectiveness of probiotic supplementation beyond merely improving dysbiosis in such infants.

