### 2.9. Sample Size Calculation

A sample size of 30 per group (total 60) was considered adequate to detect a 1.5-fold difference in alpha diversity with 80% power and a significance level of 0.05. By focusing on biological relevance, this sample size ensures that even subtle changes in microbial composition can be detected, providing a robust foundation for understanding the underlying biological mechanisms. This sample size allows for the detection of biologically meaningful variations in microbial composition, ensuring that differences in diversity metrics, such as Shannon diversity or Bray–Curtis dissimilarity, are statistically significant. By focusing on these well-defined biological parameters, this study can reliably capture important variations in microbial communities, providing a strong foundation for understanding their role in the system under investigation [21,22,23].

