### 2.14. Safety Monitoring

This will be assessed by monitoring for abdominal distension, vomiting, and diarrhea, leading to the cessation of supplementation. The risk of probiotic sepsis is rare, as reported in a recent systematic review [31]. To the best of our knowledge, probiotic sepsis has not been reported in healthy full-term infants in the literature. Moreover, probiotic sepsis (with Bifidobacteria) is easy to detect with blood culture and treat with routine antibiotics like penicillin and vancomycin. Fatality due to probiotics in preterm infants has not been reported so far, except for two cases, including one where death was attributed to a contaminated probiotic product [31]. In the second case, it was unclear whether death was ‘associated with’ or ‘due to’ probiotic sepsis (https://www.fda.gov/safety/medical-product-safety-information/risk-invasive-disease-preterm-infants-given-probiotics-formulated-contain-live-bacteria-or-yeast; accessed on 23 September 2024).

The risk of probiotic sepsis and associated morbidity is minimised by the independent microbiological assessment of the probiotic under investigation, the ability to detect bifidobacteria in blood culture using our routine blood culture assessment, and the susceptibility of probiotic bacteria to prescribed antibiotics for late-onset sepsis.

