### 3.7. Statistical Analysis of Clinical, SCFA, Bile Acid and Microbiome Data

Analysis will be based on the intention-to-treat principle. The continuous data will be summarized using median, interquartile range, and range. The categorical data will be summarized using frequency distributions. Univariate comparisons for the continuous data will be made using the Mann–Whitney test. For the categorical data, the Chi-square or Fisher exact test will be used.

The SCFA data will be analysed using a linear mixed model effect (LME) test to assess the differences between the groups over time. In this analysis, the subjects will be modelled as a random factor, and time and treatment are fixed factors. All the tests will be two-sided, and a *p*-value < 0.05 will be considered significant. The data on clinical outcomes will be analysed using SPSS version 22.0 statistical software (Armonk, NY, USA: IBM Corp.) and SCFA in R (version 3.5.1).

**Pre-planned subgroups:** (1) Infants who are born through caesarean section due to increased risk of gut dysbiosis. (2) Infants born to mothers with diet-controlled vs. insulin-dependent GDM. (3) Infants born to mothers with GDM and a normal vs. high BMI.

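### The Discussion presents the trial as an adequately powered evaluation of probiotic sepsis risk, but zero cases in 30 exposed infants would still allow a risk of about 10%

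*Protocol article*

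**What the plan says.** Section 4 (Discussion) opens by calling the trial, to the authors' knowledge, the first adequately powered placebo-controlled randomised trial "evaluating the effect of probiotic supplementation on dysbiosis in infants of mothers with GDM and the risk of probiotic sepsis".

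The rest of the article treats sepsis differently:

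- **Sizing (2.9).** The only calculation concerns microbial diversity: "A sample size of 30 per group (total 60) was considered adequate to detect a 1.5-fold difference in alpha diversity with 80% power". No sepsis rate, margin or precision target is given.
- **Aim and outcomes (2.1, 2.10, 2.11).** The aim and hypothesis concern faecal microbiome composition. The primary outcome is microbiome composition. The secondary outcomes are short-chain fatty acids, bile acids, growth and development. Sepsis appears in none of them.
- **Expected frequency (2.14).** "The risk of probiotic sepsis is rare, as reported in a recent systematic review". The same paragraph adds that the authors know of no reported case in healthy full-term infants.
- **Safety monitoring (2.14, 2.15).** "This will be assessed by monitoring for abdominal distension, vomiting, and diarrhea, leading to the cessation of supplementation". Section 2.14 also relies on routine blood culture being able to detect bifidobacteria, requires all adverse events to be recorded and assessed, and classes events leading to hospitalisation as serious. Under 2.15 the data and safety monitoring committee reviews every serious event as it occurs.

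**The concern.** The Discussion sentence joins two objects, dysbiosis and sepsis risk, under one description of the trial as adequately powered. On the wider reading, the trial is said to have adequate power for sepsis, and no calculation supports that. On the narrower reading, the power statement covers dysbiosis only, but sepsis risk is still named as something the trial evaluates.

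The authors' own account of the event makes zero cases in both arms the likely result. A reader who takes the sentence at face value could then read that zero as evidence that the risk is negligible. Parents and the designers of later trials would be relying on a property that the design does not have.

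**Working it through.** **Inputs**

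- Infants exposed to the probiotic: 30 (section 2.9; the blocks of 2 and 4 in section 2.16 fit equal allocation).
- Error rate: "a significance level of 0.05" (2.9). Sidedness: "All the tests will be two-sided" (3.7).
- Sepsis risk: described as rare, with no number (2.14). The rates used below are therefore illustrative assumptions.
- Loss to follow-up: none stated in 2.9. The values 0%, 10% and 20% are assumptions, giving 30, 27 and 24 exposed infants followed.

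**Step 1. The plan's own figure.** The 30 per group can be neither confirmed nor refuted, because no standard deviation is given. Back-solving for a 1.5-fold difference on the natural-log scale, with normal quantiles:

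SD = ln(1.5) / [(1.960 + 0.842) × √(2/30)] = 0.4055 / 0.7234 ≈ 0.56,

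which is a standardised difference of about 0.72. Whatever SD was used, the calculation concerns alpha diversity and says nothing about sepsis.

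**Step 2. Upper limit after zero cases.** For 0 of n, the exact binomial upper 95% limit is 1 − 0.05^(1/n) one-sided and 1 − 0.025^(1/n) two-sided (Clopper–Pearson). The rule of three gives 3/n.

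| Exposed infants followed | One-sided | Rule of three | Two-sided |
|---|---|---|---|
| 30 (no loss) | 9.5% | 10.0% | 11.6% |
| 27 (10% loss, assumed) | 10.5% | 11.1% | 12.8% |
| 24 (20% loss, assumed) | 11.7% | 12.5% | 14.2% |

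**Step 3. Chance of seeing at least one case among 30**, 1 − (1 − p)^30:

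- p = 1 in 100: 1 − 0.99^30 = 26.0%
- p = 1 in 1,000: 1 − 0.999^30 = 3.0%
- p = 1 in 10,000: 1 − 0.9999^30 = 0.3%

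Even at 1 in 100, then, the trial would show no case about three times in four (74%).

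**Step 4. Comparison between arms.** With 30 per arm and no case on placebo, a two-sided Fisher exact test gives p = 0.052 for 5 cases on probiotic and p = 0.024 for 6. Six cases are needed for p < 0.05. If the true risks were 10% and 0%, the chance of six or more among 30 is about 7%.

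**Step 5. Numbers that would be informative.** With zero cases, a one-sided 95% limit at or below 1% needs ln(0.05)/ln(0.99) = 298.1, so 299 exposed infants. A limit at or below 0.1% needs ln(0.05)/ln(0.999) = 2,994.2, so 2,995. The first is about ten times the planned exposure (299/30 ≈ 10).

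**The case against.** The best defence is that this is one loosely worded sentence in a Discussion. The aim and hypothesis in 2.1, the objective and outcomes in the Abstract, and the outcome lists in 2.10 and 2.11 do not mention sepsis. The Conclusions in section 5 also leave it out of what the trial will deliver. No hypothesis, comparison or decision rule rests on the clause. The power statement can be attached to dysbiosis alone, and evaluating a risk can mean ordinary safety surveillance, which is planned. That a zero count would be over-read is a prediction about a later paper.

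Most of this stands, and it limits the point to wording. It does not rescue the sentence, because recording events as they arise is monitoring and does not evaluate a rare risk.

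Two stronger readings are tempting, and the article does not support them.

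- **Sepsis risk as a stated aim that the design fails.** A reader might infer this from the Discussion, but section 2.1 sets the aim and does not include sepsis.
- **Sepsis as unmonitored.** A reader might infer this because the items listed for the bi-weekly calls are gastrointestinal symptoms, crying and sleep. But section 2.14 records all adverse events and treats hospitalisation as serious, and section 2.15 sends serious events to the committee. A case leading to admission would meet that definition. A condensed article also need not print the whole call script.

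**Conclusion.** The claim is wrong as written, and the correction is small. The trial is sized for alpha diversity only, and 30 exposed infants cannot evaluate a risk that the article itself calls rare. With no case observed, the data would remain compatible with a risk of up to 9.5% (one-sided) or 11.6% (two-sided).

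These limits assume that all 30 infants receive the product and are followed, that every case is captured, and that infants are independent. Loss to follow-up widens the limits. So would positive correlation within twin pairs, whose members section 2.16 counts as separate participants. The true risks in steps 3 and 4 of the working are illustrations, since the article gives no rate. The 1-in-100 figure is hard to square with an event called rare and is, if anything, generous to the trial.

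The point concerns what the article claims. It is not a finding against the aim, the analysis or the existence of safety monitoring. That 30 per group cannot be reproduced without a standard deviation is a separate matter and does not affect this conclusion.

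**What to change.** In section 4, delete the clause on sepsis risk and limit the power statement to the alpha-diversity target in 2.9. Add a sentence on these lines: probiotic sepsis is monitored as a safety event through adverse-event recording and committee review (2.14, 2.15); it will be reported as counts per arm with an exact upper 95% limit; and a trial of this size can neither establish nor exclude a rare risk.

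The cost is one edited sentence, one added sentence and one interval in the report. Sample size, treatment and schedule do not change. The downside is a less favourable claim for the trial.

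An optional refinement is to ask in the bi-weekly call about hospital visits or evaluation for sepsis since the last contact. The listed items do not name these, and most of the four months of supplementation takes place at home. It would make the count easier to defend, but all adverse events are already to be recorded, so the correction does not depend on it.

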## 5. Conclusions

We believe our innovative trial assessing the effects of probiotic supplementation on dysbiosis in the infants of mothers with GDM will provide robust data on gut microbiota, faecal short-chain fatty acids, long-term growth, and neurodevelopmental outcomes to guide adequately powered robust RCTs in this field.

## Figures and Tables

**Figure 1 microorganisms-13-00112-f001:**
[figure not shown]
Study design (GDM: gestational diabetes mellitus; SCFA: short-chain fatty acid; ASQ: Ages and Stages Questionnaire; HC: head circumference; T1: first week of life; T2: after 4 months of probiotics supplementation; T3: at 12 months of age; T4: at 24 months of age).

## Data Availability

The original contributions presented in this study are included in the article. Further inquiries can be directed to the corresponding authors.
